^32^ Building on this evidence, we seek to examine whether engaging in RNT prior to CBM-I, proposed to activate interpretation bias, will moderate the effects of CBM-I on interpretation bias, RNT and psychological distress. Although the attention bias literature points to a potential beneficial effect of prior RNT, it must be considered that Kuckertz *et al*^29^ focused on social anxiety rather than RNT. RNT, especially in its typical verbal form, depletes attentional control.^33–35^ Thus, it is possible that worrying or ruminating prior to CBM-I may hinder beneficial effects of training. Furthermore, effects of prior RNT may differ for the two diagnostic groups. As the first multisession study to test the proposed moderating role of RNT prior to training, we compare CBM-I with an induced period of RNT before training to CBM-I without such an induction (ie, standard CBM-I). Based on memory reconsolidation studies showing it is necessary to allow 10 min after reactivation for reconsolidation processes to be initiated (see ref. 30), participants in the condition with an induced period of RNT will engage in RNT on a recent RNT topic, followed by CBM-I relating to various worry or rumination topics (see also the Experimental conditions section). To further augment the impact of prior RNT on training, we then present CBM-I materials matched in content to participants' current RNT topic 10 min after their period of RNT. Participants in the standard CBM-I condition will be asked to indicate a recent RNT topic without subsequently engaging in RNT, and will also receive tailored CBM-I materials 10 min after completing a neutral (non-RNT) task.

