### Procedure

Participants will be invited to take part in a research study into worry and rumination which includes two face-two-face study visits scheduled 3 weeks apart, nine homework sessions to be completed online between study visits and a follow-up questionnaire to be completed online 1 month after the second study visit (see figure 2 for participant flow through the components of the study). Prospective participants will be recruited from the community and from King's College London. They will complete an initial screening questionnaire online, including the PSWQ, RRS, PHQ-9 and GAD-7. If they meet inclusion criteria, the SCID will be completed by a trained researcher to confirm a diagnosis of GAD or depression. Once enrolled, participants will complete a presession questionnaire including standardised measures (PSWQ, RRS, PHQ-9, GAD-7, RNTQ) as well as demographic information online within 24 hours prior to the first study visit (experimental session). Should participants indicate risk to themselves (a score of >1 on PHQ-9 suicidal ideation item) on the preassessment questionnaire, this will trigger a risk assessment at the study visit.

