Up to 24 hours before returning for their second study visit, participants will again complete the presession questionnaire (PSWQ, RRS, PHQ-9, GAD-7, RNTQ), and additionally will complete a ‘negative events form’ in relation to the previous 3 weeks to assess incidence of mental health-related events (eg, deterioration in symptoms, suicidal intent, hospitalisation, etc). Any events reported will be addressed with the participant at the second study visit; events may also be captured during other points of the study and will be addressed with the participant when they are raised. If the event is related to an aspect of the study, an adverse events form will be generated, which will be reviewed by the Research Steering Committee. At the second study visit, participants will again provide written informed consent for this visit, will complete treatment expectancy and acceptability ratings, assimilation and imagination ratings (in reference to the past nine sessions), and will then complete the scrambled sentences test, classic and emotional Stroop task, recognition memory test and breathing focus task before being debriefed and partially paid for their participation to date. One month after their second study visit, participants will complete the follow-up questionnaire online, which is identical to the presession questionnaire for study visit 2, and receive the final payment for their participation. The experimenter will contact participants for further information should any negative events and/or mental health-related events be reported at follow-up. Participants will receive £130 for their participation in the study.

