### Statistical methods

Statistical analyses will be carried out in Stata V.14 (StataCorp. Stata Statistical Software: Release 14. 2015, College Station, Texas, USA: StataCorp LP) and MPlus.^62^ All variables will be described by diagnostic group, experimental condition and assessment time point. In addition, assessments of feasibility and acceptability in terms of recruitment, drop-out and rate of completion will be summarised, and additional measures relating to the experimental materials will be evaluated to check the manipulations worked as intended.

As this experimental study is designed to test hypotheses regarding the causal role of interpretation bias in worry and rumination in GAD and depression, analyses will be conducted using data from ‘completers’ only, defined as participants who complete ≥8/10 sessions (percentage judged to be an adequate ‘dose’ in previous multisession CBM-I studies^25^
^26^) and who return for the second study visit within 1 month of their first visit.

To consider differences between GAD and MDD diagnostic groups that received tailored training materials, we will specify multigroup models with diagnostic group as grouping variable. We will test whether parameters differ significantly between the two diagnostic groups. Further, we can examine significant effects within each diagnostic group. Predictors in each model are experimental condition (CBM_RNT, CBM_STAND, CONTROL) and time point (study visits 1, 2 and follow-up; follow-up for questionnaire measures only).

We will examine effects on measures of interpretation bias to assess whether the CBM-I conditions are successful in training positive interpretations (near transfer). We will then assess effects on measures of RNT (self-report and behavioural) as well as anxiety and depression to investigate the impact of our CBM-I conditions on changing RNT, anxiety and depressive symptoms (far transfer). Further, we will examine whether the extent of change on self-report measures of anxiety and depression falls within the range of reliable change, defined as a reduction in scores exceeding the reliable change index for that measure. We will supplement the above analyses with disorder-specific analyses, examining the effects on near transfer for disorder-specific items only (see the Interpretation bias measures). We will control for differences in demographic variables as appropriate by including them as covariates in analyses.

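### Reliable change on PHQ-9 and GAD-7 is defined for improvement only, among completers, so reliable deterioration by condition is not a planned result

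*Protocol article*

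**What the plan says.** After setting out the group-level models, Statistical methods adds that the authors will examine "whether the extent of change on self-report measures of anxiety and depression falls within the range of reliable change", which is "defined as a reduction in scores exceeding the reliable change index for that measure". The measures concerned are PHQ-9 and GAD-7, the secondary outcomes. The same section restricts the analyses to completers, meaning participants with at least 8 of 10 sessions who return for the second visit within a month of the first.

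The questionnaires are collected three times (Procedure). Before visit 1, "participants will complete a presession questionnaire including standardised measures (PSWQ, RRS, PHQ-9, GAD-7, RNTQ"). Before visit 2, "participants will again complete the presession questionnaire (PSWQ, RRS, PHQ-9, GAD-7, RNTQ"). One month later, "participants will complete the follow-up questionnaire online, which is identical to the presession questionnaire for study visit 2".

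Two other provisions touch on worsening. A negative events form is completed before visit 2 and again at follow-up "to assess incidence of mental health-related events (eg, deterioration in symptoms, suicidal intent, hospitalisation, etc"). Under Monitoring adverse events, marked and lasting symptom increases count as adverse events if they are related to participation. They go to the Research Steering Committee at the end of the study.

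On the direction of the RNT effect, Background and rationale says "it is possible that worrying or ruminating prior to CBM-I may hinder beneficial effects of training", and Hypotheses leaves open whether prior RNT strengthens or weakens training.

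**The concern.** An individual-level index exists to show what a group mean cannot: how many people changed by more than measurement error. Here it looks in one direction only. A participant whose PHQ-9 or GAD-7 rises by more than the index meets no defined criterion and would simply be absent from the count of reliable changers.

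This matters more than usual because of the design. Participants in the CBM_RNT condition, all with diagnosed GAD or depression, are asked to worry or ruminate at the start of each of 10 sessions, and the effect of doing so is an open question in both directions. Two conditions could show the same number of reliable improvers while differing in the number reliably worse, and the planned descriptor could not show it.

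The completers-only set adds to this. Someone who worsened and stopped before the eighth session would not enter the count even if the rule were made two-directional.

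**Working it through.** The plan states no reliable change index value, no expected rate of deterioration and no other figure on this point, so there is nothing to reproduce. The check has two parts.

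**Part 1: could reliable deterioration be obtained from any planned output?**

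- *Reliable change rule (Statistical methods).* Individual-level and score-based, but reductions only and completers only.
- *Descriptive summaries and models (Statistical methods).* All variables are described by diagnostic group, condition and time point, and the models do not restrict direction. These would show an average rise. They need not show a minority who worsen while others improve.
- *Negative events form (Procedure).* It names symptom deterioration and is not limited to study-related events. It is self-report with no score threshold. The general statement on describing all variables might be read as covering it, but no summary of events by condition is specified.
- *Adverse events (Monitoring adverse events).* Symptom increases count only if significant, prolonged and related to participation. No score threshold or summary by condition is given. Randomisation and blinding says researchers are not blind to condition, so any relatedness judgement they make is not blind either.
- *Raw data (Procedure).* PHQ-9 and GAD-7 are available before visit 1, before visit 2 and at 1 month, so a score-based count in either direction can be computed.

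No planned output gives the count, and the data to produce it are already collected.

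**Part 2: how much could the count show?**

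Inputs: 20 participants per condition in each diagnostic group (Sample size), hence 20 × 2 = 40 per condition with both diagnoses pooled. The true rate of reliable worsening, p, is an assumption, shown at 5%, 10% and 15%.

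Expected number worsened, n × p, with n = 40: 40 × 0.05 = 2; 40 × 0.10 = 4; 40 × 0.15 = 6.

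Chance of seeing at least one case, 1 − (1 − p)^n:

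- n = 20: 1 − 0.95^20 = 0.642; 1 − 0.90^20 = 0.878; 1 − 0.85^20 = 0.961.
- n = 40: 1 − 0.95^40 = 0.871; 1 − 0.90^40 = 0.985; 1 − 0.85^40 = 0.998.

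One-sided 95% upper limit if no case is seen, 1 − 0.05^(1/n):

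- n = 20: 13.9%.
- n = 40: 7.2%.

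Power to separate two conditions at assumed rates of 5% and 15% (two-sided 5% test, normal approximation with pooled variance under the null):

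- n = 20 per condition: about 0.18.
- n = 40 per condition: about 0.32.

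If two conditions had equal numbers of improvers but 2 and 6 reliably worsened, an improvement-only rule would return the same result for both, and a three-category table would show the difference. The power figures mean that such a table describes and does not test.

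**The case against.** The case for leaving the plan alone has substance. The hypothesis is a reduction in distress, so an improvement-only criterion is a legitimate efficacy descriptor. It is an add-on to secondary outcomes, and the main models already run in both directions. Worsening also has its own routes in the negative events form and adverse event reporting. A condensed article may leave the rows of a descriptive table to an analysis plan that is not shown.

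Much of this stands, and it rules out several stronger readings:

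- A reader might infer that worsened participants go unreported. The documents do not support that: deterioration is asked about at visit 2 and follow-up, and study-related increases are reported to the Research Steering Committee.
- A reader might infer that the authors expect RNT induction to make symptoms worse. The passages that say it may hinder training, or be detrimental in one disorder, concern the size of the training benefit. They do not predict deterioration.
- A reader might see a contradiction between change that "falls within the range of reliable change" and change exceeding the index. There is none, because the same sentence defines the range as the region beyond the index.
- A reader might say the plan classes worsened participants as unchanged. It sets out no classification of those who do not improve.

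The appeal to an unseen analysis plan does not dispose of the point. The article does more than leave the definition open: it fixes it in one direction, and an analysis plan that follows it inherits the gap. The event routes do not replace a score-based count by condition, for the reasons in the working.

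**Conclusion.** The point holds in a limited form. Reliable change on PHQ-9 and GAD-7 is fixed as improvement only, within a completers-only set, and reliable deterioration is not a planned result by condition. The plan is incomplete here as a summary of individual change. The efficacy descriptor itself is not wrong, and no sample size, error rate or primary analysis is affected.

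The size cannot be taken from the documents. Under the assumed 5% to 15%, 2 to 6 of 40 per condition would be reliably worse; pooling the diagnoses to reach 40 is for illustration, since the plan models them as separate groups. Even a complete count would be imprecise. The rule covers anxiety and depression only, so reliable change in worry or rumination lies outside it in both directions.

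**What to change.** Apply the same reliable change index in both directions. Classify each participant on PHQ-9 and on GAD-7 as reliably improved, no reliable change or reliably worsened, at visit 2 and at 1-month follow-up. Tabulate the three categories by condition and diagnostic group, for completers and also for everyone with a baseline and a later score regardless of sessions completed. Label the table descriptive and give exact intervals with the counts, so that a zero in a cell of 20 is not read as absence of deterioration.

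The cost is one extra column in a descriptive table and a second version of it for the wider set. No new data, sample size change or error-rate adjustment is needed. The article says data collection was still under way at submission, so the rule could be set before the final analysis.

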### Hypotheses

For both diagnostic groups, we predict that CBM-I with and without prior RNT will reduce negative interpretation bias, RNT (levels of worry and rumination) and psychological distress (levels of anxiety and depression) relative to the active control condition. Furthermore, we examine whether an induced period of RNT prior to CBM-I either enhances the effects of training (by activating underlying cognitive biases, as in attention bias research), or reduces training effects (potentially due to the additional demands placed on attentional control resources by RNT). Finally, and crucially given its proposed underlying role, we expect that effects of CBM-I on worry and rumination, anxiety and depression will be driven by changes in interpretation bias.

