To examine the mediating role of interpretation bias, we will conduct mediation analyses using Baron and Kenny's^63^ approach. Depending on the final sample size and distribution of the data, bootstrapped SEs and bootstrapped CIs will be estimated.

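### Mediation is tested by the Baron-Kenny steps with only a conditional bootstrap, which can lose much power; separately, visit-2 bias is measured after the visit-2 questionnaires, so that pairing has the wrong time order

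*Protocol article*

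**What the plan says.** The Hypotheses section introduces the mediation claim as crucial: "we expect that effects of CBM-I on worry and rumination, anxiety and depression will be driven by changes in interpretation bias".

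The Statistical methods section gives the analysis in two sentences. The first is "To examine the mediating role of interpretation bias, we will conduct mediation analyses using Baron and Kenny's" approach. The second is "Depending on the final sample size and distribution of the data, bootstrapped SEs and bootstrapped CIs will be estimated". It does not say which quantity is bootstrapped, or that a test of the indirect effect replaces the causal steps.

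The Procedure section fixes the order of measurement:
- Questionnaires at visit 2: "Up to 24 hours before returning for their second study visit, participants will again complete the presession questionnaire". These are the worry, rumination, RNT, depression and anxiety scales.
- At the visit itself, participants "will then complete the scrambled sentences test, classic and emotional Stroop task, recognition memory test and breathing focus task before being debriefed".
- Follow-up: "One month after their second study visit, participants will complete the follow-up questionnaire online".

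The Sample size section plans 20 participants per condition in each diagnostic group. Its calculation concerns the breathing focus task. No power figure is given for mediation.

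**The concern.** Two separate features weaken the test of the study's mechanism.

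**Method.** The causal-steps approach asks for a significant effect of condition on outcome, of condition on mediator, and of mediator on outcome given condition. The first requirement is not needed for an indirect effect to exist. When the effect runs wholly through bias, the total effect is the product of two paths and so is smaller than either. The test can then fail although mediation is real. Interval estimation of the indirect effect would avoid this, but the bootstrap is left to a decision taken after the data are seen.

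**Time order.** If visit-2 bias is used to explain the visit-2 questionnaires, the outcome was recorded before the mediator. An association found there could equally arise in form if symptom relief made interpretations less negative. At stake is whether a positive result supports the causal claim, and whether a negative one counts against it.

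**Working it through.** **Inputs from the document.** With 20 per condition per diagnosis, the contrasts are 20 v 20 (one CBM-I arm against control), 40 v 20 (both CBM-I arms against control, one diagnosis) and 80 v 40 (both diagnoses pooled). The significance level is 0.05, taken as two-sided. There is no planned mediation power to reproduce; the stated 49 per diagnostic group is for the breathing focus task.

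**Assumed, not in the document.** Path a (condition to bias) = 0.8 SD, path b (bias to outcome) = 0.5, no baseline adjustment.

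**Model.** M = aX + e and Y = c′X + bM + √(1 − b²)·u, with e and u standard normal, so the within-arm variance of M and of Y is 1. Total effect c = c′ + ab. Under full mediation c′ = 0 and c = 0.8 × 0.5 = 0.40.

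**The binding requirement.** The noncentrality for the total effect is c / √(1/n₁ + 1/n₂).
- 20 v 20: 0.40 / 0.316 = 1.26, power about 23%.
- 40 v 20: 0.40 / 0.274 = 1.46, power about 30%.
- 80 v 40: 0.40 / 0.194 = 2.07, power about 54%.

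The steps cannot do better than this, whatever the power of the other paths.

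**Simulated power.** Causal steps means c, a and b are all significant; two paths means a and b only.

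| Contrast | Full mediation (c = 0.4): steps | two paths | Total effect d = 0.8 (c′ = 0.4): steps | two paths |
|---|---|---|---|---|
| 20 v 20 | 19% | 62% | 48% | 62% |
| 40 v 20 | 30% | 83% | 70% | 81% |
| 80 v 40 | 52% | 98% | 97% | 98% |

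Repeat runs moved these by about 1 to 2 points. The loss under full mediation is 43, 53 and 46 points. With d = 0.8 it is about 14, 11 to 12 and 1 to 2 points.

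**Sensitivity.** With b = 0.39 and full mediation (c = 0.31), the steps give 10%, 16% and 35%, against 49%, 71% and 98% for the two paths. Over a = 0.5 to 1.0 and b = 0.3 to 0.5, the steps give 2–30% at 20 v 20 and 3–41% at 40 v 20, against 15–79% and 28–94%.

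**Does a bootstrap match the two-path test?** At a = 0.8, b = 0.39, a percentile bootstrap of ab gives 47%, 71% and 98%, so the two-path figures are a fair stand-in.

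**Time order against the visit-2 bias tests.**

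| Outcome | When recorded | Order |
|---|---|---|
| Visit-2 questionnaires | Up to 24 h before the visit | Outcome first |
| Breathing focus task, visit 2 | Listed after both bias tests | Correct |
| 1-month questionnaires | One month after visit 2 | Correct, but after the visit-2 debrief |

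Earlier bias measures also exist. The recognition memory test is repeated after the first online session, and unresolved test trials appear in the sessions of all conditions.

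**Reverse process.** Let condition change the outcome (d = 0.8 to 1.0) and the outcome change bias (slope 0.39 to 0.5), with no effect of bias on the outcome. The causal steps still declare mediation in 9–29% of trials (20 v 20), 16–43% (40 v 20) and 36–72% (80 v 40). The two-path test does so in 11–30%, 17–43% and 36–72%. Changing the test therefore repairs power but not direction; only time-ordered pairs address that.

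**The case against.** Three objections have force.

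1. **The article does not fix the pairing.** It names no mediator measure, outcome or time point for mediation, and a condensed article may leave these to the analysis plan. A reader might infer that the study cannot show that bias change drives RNT change. The document does not support that. The breathing focus task is a primary RNT outcome and the basis of the sample size, and it follows both bias tests. The 1-month questionnaires also follow them, and earlier bias measures are collected. The order problem stands only for visit-2 bias with visit-2 questionnaires.

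2. **The power loss depends on the inputs.** A reader might infer that a negative mediation result is to be expected even if mediation is complete. That rests on assumed paths and mostly on within-diagnosis samples. The plan anticipates a large effect and a multigroup model; with d = 0.8 and diagnoses pooled, the steps reach 97%. What stands is that the steps never gain power over the two-path test and can lose a great deal.

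3. **The bootstrap sentence may already mean the indirect effect.** In a mediation paragraph that is the natural reading. It still makes the bootstrap conditional and leaves the steps as the named method.

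A reader might also take a positive visit-2 result as equally compatible with both directions. Condition is randomised and the control is closely matched, and nothing shows the two to be equally likely. The supportable statement is that this pairing cannot tell them apart.

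**Conclusion.** The point holds in limited form. The named method adds a requirement that the hypothesis does not need, and the remedy is left conditional on the data. Under assumed full mediation with paths 0.8 and 0.5, this costs about 43 to 53 points of power; with a total effect of d = 0.8 it costs about 14 points at 20 v 20 and almost nothing with both diagnoses pooled. The effect sizes are assumptions, and baseline adjustment was not modelled.

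The timing fault follows directly from the Procedure section and needs no assumption about effect size. It is confined to the visit-2 questionnaires paired with visit-2 bias. The change should be made because it strengthens the test of a central hypothesis at little cost; it does not invalidate the design.

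**What to change.** - **Test.** Make the indirect effect (product of the two paths) with a bootstrap confidence interval the mediation test in all cases, with no requirement of a significant total effect. Adjust for baseline mediator and baseline outcome.
- **Main time-ordered pairs.** Use visit-2 bias to the breathing focus task (same visit, before the debrief). For the visit-2 questionnaires, use recognition bias after session 1, or in-session test trials from sessions completed before the questionnaire.
- **Supportive.** Visit-2 bias to the 1-month questionnaires, because follow-up comes after participants are debriefed.
- **Association only.** Visit-2 bias with visit-2 questionnaires, with the reverse model as a sensitivity check.

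**Cost.** Wording and slightly more analysis. The variables are already part of data collection and MPlus is already named, so the participants who had completed the study by submission are not affected. The limits should be stated. Recognition bias after session 1 reflects one of ten sessions. The breathing focus task covers RNT but not anxiety or depression. Correct time order does not remove confounding between mediator and outcome.
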